## Abstract

**Introduction:**

Active self-management by patients following acute coronary syndrome (ACS) can reduce recurrent events. Patient education for transitioning from hospital to home promotes effective self-management but can be limited in the acute setting due to time and resource pressures. Patients from ethnic minority and immigrant backgrounds face additional language, cultural and health literacy barriers to receiving patient education. Self-administered virtual patient education presents an innovative solution to these challenges. This study aims to evaluate a co-adapted, virtual avatar nurse-guided, discharge education application (app) for Chinese-speaking patients following ACS.

**Methods and analysis:**

This multicentre, assessor-blinded, randomised controlled trial will recruit 98 Chinese-speaking inpatients following ACS with evaluation at 1 and 3 months postdischarge. Control participants in the control group will receive the usual ward-based patient discharge education. Intervention participants will additionally receive the education app installed on their devices before hospital discharge with unlimited access during the study period. Cultural relevance and linguistic accuracy for this Chinese version of an existing app were ensured through co-adaptation with Chinese-speaking consumers; the primary outcome will be coronary heart disease (CHD) knowledge, and secondary outcomes will include knowledge, attitudes and beliefs regarding heart attack symptoms and responses, CHD self-management behaviours, utilisation of healthcare services and quality of life. A process evaluation will be conducted alongside the trial to assess the acceptability and feasibility of the app. Between-group comparisons will be made using 95% CIs, accounting for baseline differences using linear mixed effects or mixed effects logistic regression models.

**Ethics and dissemination:**

The Western Sydney Local Health District Human Research Ethics Committee has approved this study protocol (26 February 2024, amendment number 2) (2024/STE00147), with site-specific authorisations obtained from each participating hospital. The results will be disseminated through peer-reviewed journal articles and presentations at scientific conferences.

**Trial registration number:**

ACTRN12624000408583.

STRENGTHS AND LIMITATIONS OF THIS STUDYThis is the first multicentre design randomised controlled trial to evaluate a co-adapted virtual discharge education app for patients following a heart attack in Australia.The intervention is linguistically and culturally co-adapted with consumers, delivered digitally, allowing scalability and accessibility for diverse patient populations.Mixed quantitative and qualitative process evaluation provides insights for future implementation of the intervention.Blinding of participants and clinicians is not possible due to the nature of the intervention, which may introduce performance bias.The study is limited to hospitals in metropolitan Sydney, which may affect external validity for other regions or healthcare systems.

## Introduction

 Coronary heart disease (CHD) is a leading cause of death and disease burden globally. The incidence and prevalence of CHD are projected to increase by 116% and 106%, respectively, by 2050.^1^ Despite advancements in medical technology that have improved the survival rates from coronary events, 20%–30% of patients are rehospitalised within 30 days of discharge,^2^ and >30% die within 18 months of the initial event.^3^ These statistics emphasise the critical importance of secondary prevention in reducing readmissions and overall health burdens. Additionally, heart attack survivors often experience heightened fear of recurrence and uncertainty, contributing to unnecessary distress and slower recovery.^4^

Secondary prevention of CHD is often suboptimal,^5^ particularly among patient groups from ethnic minority and immigrant backgrounds. Global migration is increasing and magnifying this issue. Chinese immigrants represent the third-largest immigrant population globally^6^ and for those living in Western countries, there are poorer CHD secondary prevention and outcomes. The Chinese-born population is the fastest-growing overseas-born group in Australia, reaching 655 790 people, a 51.7% increase in the last 10 years.^7^ This growth places it as the third largest migrant group, after the UK and India, and the largest migrant group from non-English-speaking background. A meta-analysis has found mortality rates are 30% and 80% higher than those of white and South Asian populations.^8^ Mortality and recurrence are potentially preventable if patients understand the condition, possess self-management skills and actively engage in secondary prevention behaviours.^9^

Patient education, starting predischarge, is fundamental to success in secondary prevention. Extensive evidence has demonstrated that patient education can reduce cardiovascular risk factors, mortality and morbidity.^10^,^12^ Despite this, many immigrant patients, including Chinese immigrants, do not benefit fully from these strategies due to inequitable accessibility. Language barriers are particularly significant for older Chinese immigrants. For instance, in Australia, approximately 70% of older Chinese immigrants report inadequate English proficiency.^13^ This percentage with limited proficiency increases with age and is a barrier to using mainstream patient education programmes, predominantly delivered in English.^14 15^

Cultural differences and low health literacy pose additional challenges to accessing education programmes and learning.^13 16^ Most patient education programmes fail to consider these specific needs of immigrant patients,^17^ leading to significant barriers in accessing healthcare services.^18^ Although there are translated materials, quality is often inconsistent, and there is a lack of cultural relevance to Chinese-speaking patients.^17^ The absence of a systematic and rigorous approach to developing culturally and linguistically appropriate education resources has been noted as a significant gap in the current health literature.^19 20^ The effectiveness of education interventions is also limited by a lack of research and consumer engagement in developing materials addressing the unique needs of Chinese immigrants.

To address these issues and better engage Chinese-speaking populations, culturally and linguistically appropriate patient education interventions that accommodate lower health literacy levels of patients are urgently needed.^21^ One promising approach is the use of avatar technology, which combines computer-generated imagery and practical effects to communicate in natural ways.^22^ Avatars, which are simulated human characters, can engage users through facial expressions, body language, speech and natural language understanding.^23 24^ The technology has been successfully implemented in education interventions for patients managing heart failure,^24^ diabetes mellitus,^25^ mental health^26^ and obesity.^27^

Despite its potential, few interventions using avatar technology have been adapted and evaluated rigorously in Chinese-speaking patients with CHD. This study aims to address this gap by testing a linguistically and culturally co-adapted virtual nurse-guided discharge education app specifically designed for Chinese-speaking patients with ACS.

## Methods and analysis

### Study design

This study is a prospective, outcome assessor-blinded, multicentre, randomised controlled trial (RCT) of a discharge education app for Chinese-speaking patients with ACS that uses a virtual avatar nurse to guide users (figure 1). The trial will compare this app plus usual care with usual care alone in Chinese-speaking patients with ACS. A process evaluation will be conducted following the RCT. This study protocol was developed following the Standard Protocol Items: Recommendations for Interventional Trials Checklist.^28^ The trial has been prospectively registered with the Australia and New Zealand Clinical Trial Registry (ACTRN12624000408583).

**Figure 1 F1:**
[figure not shown]
Overall project flow diagram. CHD, coronary heart disease; QoL, quality of life.

### Setting and recruitment

This study will be conducted at three large tertiary public hospitals in metropolitan Sydney, Australia, which serve large populations with diverse social, economic and cultural backgrounds. China-born residents rank among the top overseas-born groups in the catchment area of these hospitals. The care provided in these hospitals is funded by Medicare-Australia’s universal health insurance scheme.

Cardiology ward staff who are not part of the research team will screen the admission lists of the wards at the participating hospitals to identify potential participants. A bilingual researcher will approach the potential participants to explore their interest in participating. Following informed consent, patients will be enrolled in the study and complete a baseline assessment by the bilingual researcher before randomisation. The baseline assessment will include participants’ demographic (age, gender, education, English proficiency, health literacy, marriage status, employment status, technology use) and clinical data (admission diagnosis, comorbidities). Patients who are ineligible or decline to participate will be recorded, and the reason for exclusion or refusal will be documented. Recruitment is anticipated to take place between 1 July 2024 and 31 August 2026.

### Participants

Inclusion criteria are:

adults (≥18 years) admitted to the participating hospitals with a diagnosis of ACS (unstable angina, non-ST-elevation and ST-elevation myocardial infarction);being discharged home;Chinese (Mandarin)-speaking;having a personal smartphone/tablet computer with software capable of downloading the app.

Exclusion criteria are:

critically unwell or have severe co-existing medical conditions that would impede or prevent engagement in lifestyle behaviour change, for example, dementia or terminal illness;unable to understand, speak or read basic Chinese to consent;sufficient vision, manual dexterity or hearing to use the app.

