### Randomisation and blinding

Participants will be randomly allocated to either the intervention or control group after the baseline assessment is completed. Randomisation will be performed by a research team member independent of recruitment, data collection and analysis using Excel functions with a 1:1 ratio (intervention:control), who will also be responsible for securely keeping the allocation.

Follow-up assessors will be blinded to group allocation with no anticipated circumstances for which unblinding is required. Health professionals delivering usual care will remain blinded to the participant’s group allocation unless the participant discloses it. Due to the nature of the intervention, blinding the intervention to participants is not possible.

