#### Intervention

After baseline assessment and randomisation, a researcher who completes the baseline assessment will assist participants allocated to the intervention group with downloading and installing the app on their smartphone or tablet before hospital discharge. The researcher will ensure that the participants are familiar with the app and its functions and have access to it throughout the study period, in addition to their usual care. The participants will have unlimited independent access to all the educational modules. They will be encouraged to contact the researcher if they experience technical issues with the app during the study period.

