### Sample size calculation

Since there is no established minimally important difference in disease knowledge or similar intervention for the CADE-Q SV (Simplified Chinese), the sample size calculation is based on a mean change of 2.3 points (SD 3.6), which has been published in patients with CHD precompleting and postcompleting a comprehensive cardiac education programme.^41^ A total of 78 participants (39 per group) will be required to detect a between-group difference in CADE-Q SV (Simplified Chinese) score of 2.3 points with (α=0.05, 80% power) (calculated from https://sample-size.net/sample-size-means/). Accounting for a 20% dropout rate, 98 patients (49 per group) will be needed.

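### The third exclusion criterion is inverted: as written, being able to use the app is a reason for exclusion

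*Protocol article*

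**What the plan says.** In the protocol article, section Participants, the exclusion list has three items. The first covers critical illness or severe coexisting conditions that would get in the way of lifestyle change. The second is "unable to understand, speak or read basic Chinese to consent". The third is "sufficient vision, manual dexterity or hearing to use the app". No other section restates the third item in the opposite sense.

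The section Intervention describes what a participant in the app arm does: "The researcher will ensure that the participants are familiar with the app and its functions", and then "The participants will have unlimited independent access to all the educational modules". Intervention content describes six modules led by an avatar nurse, with interactive questions, quizzes and games. Intervention features adds that the avatar communicates by speech, facial expression and body language, and that several visual methods are used.

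Two other sections depend on the eligibility rule. Setting and recruitment says that ineligible patients are recorded with the reason for exclusion. App feasibility defines uptake as the percentage of eligible participants who enrolled.

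**The concern.** An exclusion criterion should name what keeps a patient out. The first two items do so: each describes an impediment. The third describes an ability, and it is the ability that the intervention needs. Followed as written, it turns away the patients the app is meant for.

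Eligibility is an operative rule. It decides who is entered, which reason is logged for those who are not, and who counts as eligible in the uptake percentage. It also tells a later reader to whom the results apply. A rule with the wrong sign should not stand in a protocol article under which recruitment is planned to run to 31 August 2026.

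**Working it through.** **1. The criterion against its neighbours.** Items one and two exclude for a deficit (illness, inability in Chinese). Item three excludes for a capacity. The word 'unable' in item two cannot carry over: a semicolon separates the items, and 'unable … sufficient vision' is not grammatical. The list is run together in the text at hand, but the words of the item are complete, and nothing suggests a lost prefix or a redaction.

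**2. The criterion against the intervention.** Familiarisation with the app and independent use of its modules (Intervention) presuppose a patient who can operate it. A speaking avatar, visual material, quizzes and games (Intervention content, Intervention features) draw on hearing, vision and manual control. An exclusion for having these faculties cannot be squared with those sections. An exclusion for lacking them can.

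**3. What each wording does.** Write V, D and H for adequate vision, dexterity and hearing, and consider this criterion alone.

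- As printed: exclude if V or D or H. A patient passes only if not V, not D and not H.
- With 'insufficient': exclude if not V, or not D, or not H. A patient passes only if V and D and H.

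| Patient | As printed | With 'insufficient' |
|---|---|---|
| All three adequate | Excluded | Passes |
| One or two adequate | Excluded | Excluded |
| None adequate | Passes | Excluded |

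The two groups that pass have no member in common. If the 'or' is read loosely as 'and', the printed item still excludes the patient with all three, so the conflict does not depend on how 'or' is taken.

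**4. What follows for the records.** If the printed rule were applied, the log would give adequate function as a reason for exclusion, and the uptake denominator would be drawn from the bottom row of the table instead of the top row.

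**5. Whether any planned figure moves.** The inputs are in Sample size calculation: difference 2.3, SD 3.6, "α=0.05, 80% power". The allocation is 1:1 (Randomisation and blinding). Sidedness is not stated, so two-sided is assumed.

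- n per group = 2 × (1.96 + 0.8416)² × 3.6² / 2.3² = 2 × 7.849 × 12.96 / 5.29 = 38.5, rounded up to 39, or 78 in total. This reproduces the plan.
- Power at 39 per group is 80.5% by the normal approximation and 79.5% by the t distribution.
- Dropout: 78 / (1 − 0.20) = 97.5, rounded up to 98, or 49 per group. This also reproduces the plan.

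The eligibility wording enters none of these formulas, so correcting it leaves 78 and 98 unchanged.

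**The case against.** The strongest reply is that nobody would apply the item as printed. The neighbouring exclusions and the purpose of the trial make the meaning plain, and the ethics-approved protocol and screening form, which are not shown, may already carry the right word. Much of this stands. The intended sense is evident, and harm in actual screening is not shown. The reply does not remove the fault: the article states the criterion, states it the wrong way round, and corrects it nowhere.

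A reader might be tempted to infer more than the document supports:

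- *That all 98 planned participants are ineligible, or that each one enrolled is a deviation.* This requires the printed wording to be the one used at the sites, which the document cannot establish. Setting and recruitment has ward staff screen admission lists and a bilingual researcher approach patients. It does not say who judges vision, dexterity or hearing, so differences between hospitals are conjecture.
- *That the item contradicts the device criterion, "having a personal smartphone/tablet computer with software capable of downloading the app".* That criterion concerns hardware. A person with poor vision or hearing can own such a device, so there is no logical conflict. The conflict is with use of the app.
- *That the 'or' would admit patients with only one adequate faculty.* This would be so only if the phrase were moved unchanged to the inclusion list, where the protocol does not put it. Nor does the document say which faculties are needed to complete the modules, so no claim can be made about who could not finish them.
- *That this is a poor design choice.* Nothing suggests that anyone chose to exclude capable users.

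**Conclusion.** Wrong as written: an internal inconsistency in a stated eligibility rule, most likely a drafting slip. The inverted sign is certain from the text. Its effect on the sample size and the analysis is nil. Its effect on enrolment, the exclusion log and the uptake percentage is conditional: on literal application the wrong patients would pass, and without it nothing changes. The conclusion rests on the article being the only statement of the criterion at hand, and on the reading, supported by the Intervention sections, that the app is meant for people able to use it.

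**What to change.** In the third exclusion criterion, replace the first word, 'sufficient', with 'insufficient' and leave the rest as it is. Inadequacy in any one of the three faculties then excludes, in line with the two items before it. Check that the screening form and the registry entry carry the corrected sense. If either has the printed wording, correct it and review the logged reasons for exclusion under this item.

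The cost is one word and a short check of two documents. No recalculation is needed.

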### Randomisation and blinding

Participants will be randomly allocated to either the intervention or control group after the baseline assessment is completed. Randomisation will be performed by a research team member independent of recruitment, data collection and analysis using Excel functions with a 1:1 ratio (intervention:control), who will also be responsible for securely keeping the allocation.

Follow-up assessors will be blinded to group allocation with no anticipated circumstances for which unblinding is required. Health professionals delivering usual care will remain blinded to the participant’s group allocation unless the participant discloses it. Due to the nature of the intervention, blinding the intervention to participants is not possible.

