### Study groups

#### Control

As determined by the hospitals, participants in the control group will receive usual discharge education from their doctors and other healthcare professionals, such as nurses or pharmacists. This discharge education is usually delivered by a Chinese-speaking health professional or through an English-speaking family member and provides information that summarises discharge, medications and follow-up care, such as cardiac rehabilitation. At the conclusion of the study, control participants will receive a link to download the app.

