### Statistical analysis

Statistical analysis will follow the intention-to-treat principle and a prespecified statistical analysis plan led by a blinded statistician. Descriptive statistics will be used to characterise participants. The analysis of variance (ANOVA) will be used to compare the primary outcome and estimate the mean difference and 95% CI. Furthermore, to assess whether there is a change in the outcome over time (baseline, 1 month and 3 months) within and between groups, a linear mixed effects regression model will be used with a random intercept for patients to account for individual variability. Assumptions for ANOVA and the linear mixed-effects model will be assessed prior to analysis. For ANOVA, independence, normality within groups and homogeneity of variances will be checked using Levene’s test, and outliers will be addressed if necessary. For the mixed-effects model, linearity, residual normality and homoscedasticity will be evaluated through diagnostic plots. If assumptions are violated, corrective measures such as data transformation or robust methods will be applied. In the case of missing data that are missing at random in nature, multiple imputations will be used. For secondary continuous outcomes, linear mixed effects regressions will be performed to assess whether there is change in the outcomes over time within and between groups. Similarly, for secondary categorical outcomes, mixed effects logistic regression models will be used to test for the change in the outcomes over time within and between groups.

Interview audio files will be transcribed verbatim into simplified Chinese and then translated into English by a bilingual researcher. To ensure the accuracy and reliability of the translation, another bilingual author will randomly audit five translated transcripts and back-translate these from English into simplified Chinese. The data will then be analysed using directed content analysis, with coding and theme generation facilitated by an Excel spreadsheet.

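### Each of the three hospitals sets its own usual discharge education, but the stated primary ANOVA and mixed model carry no hospital term

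*Protocol article*

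**What the plan says.** - **Sites.** Setting and recruitment: "This study will be conducted at three large tertiary public hospitals in metropolitan Sydney".
- **Comparator.** Control: "As determined by the hospitals, participants in the control group will receive usual discharge education from their doctors" and other health professionals. The same section says it usually comes from a Chinese-speaking professional or through an English-speaking family member.
- **Contrast.** Study design: "The trial will compare this app plus usual care with usual care alone in Chinese-speaking patients with ACS". Usual care is therefore the background in both arms.
- **Allocation.** Randomisation and blinding: "using Excel functions with a 1:1 ratio (intervention:control". Nothing is said on blocking or strata.
- **Primary analysis.** Statistical analysis: "The analysis of variance (ANOVA) will be used to compare the primary outcome and estimate the mean difference and 95% CI".
- **Longitudinal model.** Same section: "a linear mixed effects regression model will be used with a random intercept for patients to account for individual variability".

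The abstract adds that comparisons account for baseline differences, without naming hospital. The Statistical analysis section refers to a prespecified analysis plan, which is not shown.

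**The concern.** The primary outcome is a knowledge score and the background treatment is education. If hospitals educate differently, or serve patients with different starting knowledge, hospital predicts the outcome. The article names the primary test and the random effect of the model, and hospital appears in neither.

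What is at stake is precision. Between-hospital variation that a model could remove stays in the residual, and a chance difference in hospital mix between arms goes uncorrected. The trial has little slack: its planned evaluable number gives almost exactly 80% power.

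**Working it through.** **Inputs.** From Sample size calculation: difference 2.3 points, SD 3.6, alpha 0.05 (two-sided assumed), 80% power, 39 evaluable per group, 20% dropout, 98 enrolled. From Setting and recruitment: three hospitals. Assumed, because the documents give no figures: hospital means of 0, 0, 0; of −1, 0, +1 (2-point span); or of −2, 0, +2 (4-point span).

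**1. The plan's own figure.** n per group = 2 × (1.960 + 0.842)² × 3.6² / 2.3² = 38.5, so 39. Dropout: 39 / 0.8 = 48.75, so 49 per group and 98 in all. Both reproduce. Power at 39 per group by the noncentral t distribution is 79.5%.

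**2. Between-hospital variance, equal hospitals.** 2-point span: (1 + 0 + 1)/3 = 0.667. 4-point span: (4 + 0 + 4)/3 = 2.667.

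**3. Power with and without hospital, arms balanced within hospital.** The answer depends on what the SD of 3.6 contains, so both readings are shown. Power is from the noncentral t at 39 per group.

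| Reading of SD 3.6 | Span | SD without hospital term | SD with hospital term | Power without | Power with |
|---|---|---|---|---|---|
| within-hospital | 2 | √(12.96 + 0.667) = 3.69 | 3.60 | 77.5% | 79.5% |
| within-hospital | 4 | √(12.96 + 2.667) = 3.95 | 3.60 | 71.8% | 79.5% |
| total | 2 | 3.60 | √(12.96 − 0.667) = 3.51 | 79.5% | 81.6% |
| total | 4 | 3.60 | √(12.96 − 2.667) = 3.21 | 79.5% | 87.8% |

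The loss from omitting hospital is about 2 points of power (2-point span) or about 8 points (4-point span).

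**4. Simulation.** 78 evaluable patients, within-hospital SD 3.6, hospital sizes 26/26/26 or 39/23/16; 15,000 runs under no treatment effect and 8,000 at 2.3 points.

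- *Unstratified allocation, no hospital term:* type I error 4.7% to 5.5%. The mean shift in the treatment estimate from hospital mix is zero to within simulation error. Its 95th percentile in absolute value is 0.33 to 0.36 points at a 2-point span (0.333/2.3 = 14% to 0.363/2.3 = 16% of the target) and 0.67 to 0.73 at a 4-point span (29% to 32%).
- *Unstratified, power without and then with the term:* 76.9–77.5% and 77.6–78.4% at a 2-point span (gain 0.2 to 1.4 points); 71.2–72.0% and 77.7–78.8% at a 4-point span (gain 6.5 to 7.2). With no hospital differences, the term lowers power by about 1 point (for example 79.6% to 78.6%).
- *Stratified by hospital:* leaving the term out makes the test conservative, with type I error 4.3% at a 2-point span and 3.0–3.2% at a 4-point span. With the term it is 4.7–4.8%, and power is 79–80%.

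**5. Shift and power loss are one effect.** In a 39:39 trial without stratification, the standard error from within-hospital variation is 3.6 × √(2/39) = 0.815. At a 2-point span the chance shift has SD 0.186. Combined: √(0.815² + 0.186²) = 0.836, which is 3.69 × √(2/39). The unadjusted interval already carries the shift, so the two should not be counted as separate harms.

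**The case against.** **No hospital difference is documented.** The Control section gives one description for all sites. Delivery by a professional or through a family member could vary from patient to patient within a hospital, and all three sites are large public hospitals in one city under the same funding. This stands: the size of the effect is assumed throughout.

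**The 4-point span is generous.** The Sample size calculation takes 2.3 points as the change after a comprehensive education programme. A 4-point span between hospitals exceeds that by 70% (4/2.3 = 1.74). It is an upper case. The rise to 88% needs, in addition, that an SD borrowed from another study already contains the differences among these three hospitals.

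**A reader might infer that the list is unstratified.** The article states the tool and the ratio, and says neither that the list is stratified nor that it is not. A condensed article commonly leaves that to the full protocol, so no criticism of the allocation is made here.

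**A reader might infer that hospital differences load onto one arm.** The documents do not support that. Individual randomisation, with each hospital's usual care given in both arms, lets hospital reach the contrast only by chance, with mean shift zero and type I error near 5%.

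**The hidden analysis plan may list covariates.** It may. But the article itself names the primary test and the model's random effect, and as stated these omit hospital. If the plan already includes it, the point is settled.

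**Conclusion.** The point holds as one of precision. Hospitals determine the education that both arms receive, yet neither the stated primary ANOVA nor the mixed model includes hospital. The unadjusted analysis remains valid.

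If hospital means span 2 points, the cost is about 2 points of power when arms are balanced within hospital, and the term alone recovers somewhat less when they are not. At a 4-point span the cost is about 8 points. If hospitals do not differ, nothing is gained and up to about 1 point is lost. These figures rest on assumed hospital means, three hospitals of roughly similar or moderately unequal size, a two-sided test and 78 evaluable patients. The required sample size does not change.

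**What to change.** In the analysis plan, before unblinding, prespecify hospital as a fixed effect (two indicator terms) in the primary model and in the models for the secondary continuous outcomes. State it in the article's terms: the ANOVA becomes a two-factor model with treatment and hospital, and the mixed model keeps its patient intercept and gains the two terms.

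The cost is two degrees of freedom (76 to 74 residual with 78 patients) and a line of text. No patients, visits or changes to allocation are needed, and it can be done even if recruitment is complete. If the allocation list turns out to be stratified by hospital, the term is needed for that reason too, because omitting it makes the test conservative.
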